### Ethics and dissemination

This research was approved by the Biological and Medical Ethics Committee of Tangdu Hospital (NO. 201704-13). It was also approved by the Ethics Committee of every participating center in this study. Every adverse event will be reported to the Ethics Committee in a timely manner. Every revision of the research protocol will be reported to the Ethics Committee. The investigators will strictly follow the precepts of the Declaration of Helsinki and Human Biomedical Research Ethical Issues when conducting this study. Patient information will be kept confidential throughout the study and the publication process.

## Discussion

An intracranial aneurysm is an abnormal bulging in the wall of the intracranial artery and is the most common cause of subarachnoid hemorrhage. Subarachnoid hemorrhage, mostly caused by the rupture of an UIA, is the third most common acute cerebrovascular disease, and the associated death and disability rate can be as high as 64%. It is an urgent task to control the risk factors and reduce the rupture rate of UIAs. It is equally important to reveal the natural history of UIAs and identify the risk factors for rupture.

It has been reported by UCAS that the natural course of unruptured cerebral aneurysms varies according to the size, location, and shape of the aneurysm. The annual rupture rate of UIAs is 0.95% (95% confidence interval 0.79–1.15). Larger aneurysms and those located in the posterior and anterior communicating arteries or that have a daughter sac are more likely to rupture [9]. The ISUIA also showed that the location and size of the aneurysm are predictors of rupture. Aneurysms located in the posterior circulation and posterior communicating artery rupture more easily than those located in the internal carotid artery, anterior communicating, anterior cerebral artery or middle cerebral artery. The 5-year cumulative rupture rates of aneurysms larger than 25 mm are as high as 40–50%. The 5-year cumulative rupture rates of aneurysms smaller than 7 mm are as low as 0–2.5% [7, 8].

Although some risk factors for rupture have been identified in these two large studies, the influence of other factors, such as drug history, disease history, genetics, lifestyle and stress from life and work, remain unclear. To date, the causes underlying the development of aneurysms are equally unclear. In addition, there are no reports about the rupture rate of UIAs in the Chinese population. The present study will describe the natural history of UIAs, calculate the annual rupture rate of the entire cohort as well as specific subgroups of patients, and identify the specific subgroups that have higher risks of rupture. The conclusions will provide evidence to guide the appropriate management of UIAs and develop a more reasonable UIA prevention and control strategy in China.

An observational design was chosen for this study, in which the diagnosis and treatment of disease will not be affected. Compared with an interventional study, more patients with different characteristics can be enrolled in a real-world study that has lower internal validity but superior external validity. The results of the real-world study better represent the current status of the diagnosis and treatment of diseases. At the same time, the study can be implemented for a long period of time, include a large sample size, and provide benefits for less of an investment. Furthermore, the conclusions drawn from the study might be more easily extrapolated to and more useful in clinical practice. Lastly, registration studies are safer for the participants [15, 16]. Despite the shortcomings [17], a real-world study is still the most suitable design for this study.

The UIA research platform will be established in this study based on multicenter cooperation and will take advantage of the EDC system. There are 3 cohorts in this platform: the Cohort of Unruptured Aneurysm without Treatment (CIAP-1, CIAP-2, CIAP-3), Cohort of Unruptured Aneurysm with Treatment (CIAP-4), and Cohort of Ruptured Aneurysm (CIAP-5). The relationships among these five studies have been clearly described in the protocol of CIAP-2 and CIAP-4 [12, 13]. The patients in this study (CIAP-1) will be transferred to the cohort in CIAP-5 if the IA ruptures. They will be transferred to the cohort in CIAP-4 if the IA is surgically treated. Under these conditions, observation will be discontinued for this study. The patients in CIAP-1 will also be enrolled in CIAP-2/CIAP-3 if they meet the additional selection criteria (Figs. 1, 2).

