### Study design and methods

The China Intracranial Aneurysm Project (CIAP) is a prospective, observational registry study of the natural courses, risk factors for the onset and rupture, treatment methods, comorbidity management and other aspects of IAs. To the best of the authors’ knowledge, the CIAP, sponsored by Chinese Science and Technology Ministry and National Stroke Prevention Project Committee, is the largest ongoing project evaluating IAs in China; it currently includes 5 studies. The first study in the CIAP was designed to set up and manage a UIA database of 5000 individuals and calculate the annual rate of rupture of those aneurysms. The second study aimed to identify the risk factors for aneurysm rupture and develop a multidimensional predictive model for rupture. The third study was designed to explore the strategy of antithrombotic therapy in UIA patients complicated by ischemic cardiovascular/cerebrovascular diseases. The fourth study was designed to compare the therapeutic effects of intervention surgery and craniotomy surgery in the treatment of UIAs. The fifth study was designed to develop a standardized clinical pathway for early-stage cerebral hemorrhage caused by aneurysms [12, 13].

CIAP-1, intended to establish an open research platform and a nationwide UIA cohort, is the first and most fundamental task of the entire project. It is designed to achieve the following aims:Establish a nationwide public health and research platform administered by researchers, doctors, clinical center managers, Contract Research Organizations (CROs) and health management companies.Establish a nationwide prospective UIA cohort as a joint effort from 20 clinical centers.Clarify the natural history and annual rupture rate of UIAs in China.Identify the characteristics of people with intracranial aneurysms and look for possible causes of IAs.Screen for risk factors for UIA rupture and provide guidance to CIAP-2, which is designed to establish a multidimensional model to predict UIA rupture.

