### Participating center qualification

The investigators will collaborate with the other 19 medical centers located in the different regions of China (Southeast, Southwest, Northwest and Northeast China). Each center has more than two referral units, has experience in the diagnosis of UIAs and has a skilled treatment team. Thus, it is believed that this cohort can adequately represent the population at the regional and national levels. During the study period, all the patients included in this study will be observed and treated in the collaborating medical centers.

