### Outcomes

The primary outcome: the rupture of the aneurysm.The secondary outcome: obvious changes in the morphology of the aneurysm (maximum diameter increase ≥ 1 mm or new daughter sac forms); or a new serious clinical symptom develops (such as headache).

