### The plan and methods of follow-up

Every patient will be followed for at least 1 year if the aneurysm is not ruptured or treated by surgery. The Estimated Primary Completion Date is December 30, 2021. Thus, the follow-up procedure is expected to last until December 30, 2022. The participants will be contacted by phone or Internet at 3 months and 12 months and contacted face to face at 6 months. Images of computed tomography angiography (CTA)/magnetic resonance angiography (MRA)/digital subtraction angiography (DSA) and vascular ultrasound will be obtained at 6 months. The participants’ visit and evaluation schedule is shown in Table 1.

**Table 1 Tab1:** Participants’ visit and evaluation schedule

Visit number	Screening period	Follow-up period		
	1	2	3	4
Research arrangement	Screening	90 ± 14 days	180 ± 30 days	365 ± 30 days
Informed consent	√			
Selection criteria	√			
Baseline information	√			
History of disease and history of medicine taking	√			
Medicine taking		√	√	√
Symptoms and physical examination	√	√	√	√
Electrocardiogram	√			
Routine blood test	√			
Blood sugar	√			
Blood lipid	√			
Homocysteine	√			
Head CT/MRI	√	√	√	√
CTA/MRA/DSA	√		√	
Vascular ultrasound	√		√	
mRS score	√	√	√	√
HAMA score	√	√	√	√
End point evaluation		√	√	√
Adverse event evaluation		√	√	√

Participants should visit at least once a year after 1 year

*CT* computed tomography, *MRI* magnetic resonance imaging, *CTA* CT angiography, *MRA* magnetic resonance angiography, *DSA* digital subtraction angiography, *mRS score* modified Rankin scale score, *HAMA score* Hamilton anxiety score

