### Statistical analysis

Statistical description of the clinical data.Continuous variables are expressed as the mean ± standard deviation and compared by one-way analysis of variance. Categorical variables are expressed as the quantity (rate) and compared with the Chi-square test. Continuous variables that do not conform to a normal distribution are expressed using the median and interquartile range and are compared by the Mann–Whitney nonparametric test. P < 0.05 is considered significant.Annual rupture rate calculation.The overall annual rupture rate of UIAs is the proportion of aneurysms that ruptured in one year, which will be calculated with the data from the 1-year assessment. When analyzing the rate in a specific population, a subgroup analysis will be performed.Assessment of influential factors.Multivariate regression analysis will be used to calculate the OR of high-risk factors for the development and rupture of aneurysms. The 95% confidence interval will also be calculated. The receiver operating characteristic curve (ROC) will be used to determine the cutoff value with the best sensitivity and specificity for the prediction of rupture.

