Moreover, there is a serious over-treatment phenomenon in the treatment of UIAs in China, which might affect the accuracy and authenticity of our conclusions about the rupture rate. From another perspective, this study will provide solid evidence that can be used to control the overtreatment phenomenon in China.

In conclusion, this is the first nationwide study aimed at creating a database of UIAs and describing the natural course of UIAs in China. It will provide evidence to guide the choice of the most appropriate management for specific UIA patients with different risk factors.

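### The protocol says care is unaffected but schedules a 6-month angiogram for every patient; surgery following that scan would be informative censoring of the 1-year rupture proportion, of a size the documents cannot fix

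*Protocol article*

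**What the plan says.** The Discussion of the protocol article justifies the design this way: "An observational design was chosen for this study, in which the diagnosis and treatment of disease will not be affected". The stated aim, under Study design and methods, is to "Clarify the natural history and annual rupture rate of UIAs in China".

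The section on follow-up reads: "Images of computed tomography angiography (CTA)/magnetic resonance angiography (MRA)/digital subtraction angiography (DSA) and vascular ultrasound will be obtained at 6 months". Table 1 places this at 180 ± 30 days and ticks it for all participants. Table 1 also ticks head CT/MRI at 90, 180 and 365 days, whereas the text of the same section has the 3- and 12-month contacts made by phone or Internet.

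The secondary outcome includes "obvious changes in the morphology of the aneurysm", defined as a rise in maximum diameter of at least 1 mm or a new daughter sac. Under Participating center qualification, "all the patients included in this study will be observed and treated in the collaborating medical centers". On surgery, the Discussion says of the patients: "They will be transferred to the cohort in CIAP-4 if the IA is surgically treated", and observation in CIAP-1 then stops. Under Statistical analysis, the annual rate is the proportion of aneurysms ruptured in one year, "which will be calculated with the data from the 1-year assessment".

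On the rupture rate, the limitations in the Discussion concede that "there is a serious over-treatment phenomenon in the treatment of UIAs in China, which might affect the accuracy and authenticity of our conclusions".

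**The concern.** A repeat angiogram fixed by the study calendar is a diagnostic procedure. If the study requires it, the sentence saying that diagnosis is unaffected does not fit the schedule, whatever happens to treatment afterwards.

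The consequence for the primary result runs through treatment. The 6-month scan is the only CTA/MRA/DSA that Table 1 places between baseline and one year. The features it can reveal are related to what the Discussion, citing a large cohort, reports as rupture predictors: size and a daughter sac. The centers that do the scan also treat the patients, and no passage withholds the result from clinicians. If a finding at the scan is followed by surgery, the patient leaves the risk set because of something that also predicts rupture. A plain 1-year proportion does not correct for that.

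The limitation on over-treatment does not cover this mechanism. It points to practice in China at large, not to a decision point at a known date in the study's own schedule. At stake is whether the headline figure can be read as natural history or only as a rupture rate under scheduled imaging.

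**Working it through.** The plan gives no figure for this effect, so there is none to reproduce.

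**Share of the year after the scan** (Table 1 window):
- day 180: (365 − 180)/365 = 51%
- day 210: (365 − 210)/365 = 42%
- day 150: (365 − 150)/365 = 59%

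**Illustration of size.** From the documents: an annual rupture rate of 1% and an allowable error of 0.6 points (Sample size calculation). Assumed, not in the documents: share growing at 6 months g = 2% to 10%; rupture hazard of growers relative to others h = 5 to 10; share of growers treated at once after the scan t = 50% to 90%. Rupture risk is spread evenly over the two half-years.

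Share of ruptures in months 6 to 12 removed: s = g·h·t / (g·h + 1 − g).

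The protocol does not say how patients treated before one year enter the proportion, so three ways are shown, each in percent for a true 1.00%:
- (a) kept as non-ruptured: 0.5 + 0.5(1 − s)
- (b) censored at treatment without weights: 0.5 + 0.5r, where r = [(1 − g) + g(1 − t)h] / [(1 − g·t)(1 − g + g·h)]
- (c) left out altogether: result (a) divided by (1 − g·t)

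| g, h, t | s | (a) | (b) | (c) |
|---|---|---|---|---|
| 0.02, 5, 0.5 | 0.05/1.08 = 0.046 | 0.98 | 0.98 | 0.99 |
| 0.05, 10, 0.9 | 0.45/1.45 = 0.310 | 0.84 | 0.86 | 0.88 |
| 0.10, 10, 0.9 | 0.90/1.90 = 0.474 | 0.76 | 0.79 | 0.84 |

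The largest shifts are 0.24, 0.21 and 0.16 points.

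**Direction.** Under (a) and (b) the bias is downward or nil for any h of 1 or more. Under (b) with h = 1, r = 1 and there is none. Under (c) it is downward only if h exceeds 2(1 − g)/(1 − 2g), which is about 2.0 to 2.3 for g = 2% to 10%. Below that, leaving treated patients out raises the proportion slightly: g = 0.10, h = 1, t = 0.9 gives 0.955/0.91 = 1.05%.

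**Against precision.** If 4696 × 0.95 = 4461 patients are evaluable, the 95% half-width at 1% is 1.96·√(0.01 × 0.99/4461) = 0.29 points. The largest shift, 0.24, is below that and is 40% of the 0.6-point allowable error; 0.16 is 27% of it. In events, 1% of 4461 is about 45 ruptures, against about 44 to 34 under (a).

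**The case against.** The sentence in the Discussion contrasts an observational with an interventional study, and can be read as saying only that the study assigns no treatment. The aneurysm is already diagnosed at entry, the modality is left open, and no passage says that a 6-month angiogram departs from usual care at these centers. This is fair for the treatment half of the sentence. It does not remove the need to say whether the scan is required, because the follow-up text states without condition that images will be obtained.

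A reader might infer that the scan triggers treatment and that the rate after about day 180 is therefore not the natural course. The documents do not support that. No passage says growth leads to surgery, and the over-treatment remark is not tied to follow-up scans. There is no figure for growth, for treatment after the scan, or for imaging in usual care. Only surgery in excess of what usual care would have prompted is attributable to the schedule, whereas the illustration counts all of it. Its upper end also needs 10% growing, a tenfold hazard and 90% treated at once.

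Nor can it be said that head CT/MRI at days 90 and 365 is firmly imposed, since Table 1 sits against remote contact at those visits.

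It is also true that treatment-related distortion is disclosed in general terms, and that follow-up image changes are collected. But no stated analysis uses them for this purpose, and no data item described links an operation to the study scan.

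**Conclusion.** The point stands in limited form. The claim that care is unaffected and the scheduled 6-month angiogram need reconciling, and surgery following that scan is a possible source of informative censoring in a simple 1-year proportion, with about half of the year exposed.

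The bias is downward or nil if treated patients are kept as non-ruptured or censored without weights and growers have at least the hazard of others. Excluding them entirely can reverse the sign when the hazard ratio is below about 2. The size runs from negligible to roughly 0.2 percentage points on a true 1%, on assumptions for growth, hazard and treatment that all come from outside the documents. Nothing here shows that the effect will occur; the article describes no data item that would show whether it did.

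**What to change.** 1. Reconcile the follow-up section and Table 1 with the Discussion on whether follow-up imaging is required by the study or recorded only when done in usual care. Include the head CT/MRI that Table 1 lists at days 90 and 365 against phone or Internet contact.
2. If the 6-month angiogram is required, describe the result as the rupture rate of untreated UIAs under scheduled 6-month imaging, and say that this imaging may influence treatment.
3. Record in CRF-B the date of each surgical treatment and whether the study scan prompted it. Add a sensitivity analysis of the 1-year rate that censors at treatment, with weights built from baseline predictors and the 6-month growth finding.
4. Optionally, show rupture incidence per person-time before and after each patient's actual scan date. This is supportive description, not a replacement for the annual rate.

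Cost: protocol wording, a small CRF-B addition and some extra analysis, with no new patients or procedures. The weighted estimate will have a wider interval. The pre-scan rate would rest on about 22 expected ruptures (half of 45), so its interval is about √2 = 1.4 times as wide. The headline claim becomes narrower.

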**Fig. 1 Fig1:**
[figure not shown]
Flow chart of the CIAP. The relationships among the five studies in CIAP are described in this figure. *UIA* unruptured intracranial aneurysm, *RA* ruptured aneurysm

**Fig. 2 Fig2:**
[figure not shown]
Flow chart of CIA-1. *CRF* case report form

Taking advantage of the EDC system, it is possible to upload, browse and examine the data at the same time in different centers. The data can be centrally managed for consistent quality control. Every change in the patient’s information in the database will be recorded by the system, which will increase the reliability and credibility of the data.

Several measures have been taken to ensure that this nationwide large-scale multicenter project is implemented adequately according to the unique standards: (1) the EDC system has an instant error reporting function; (2) self-inspection is conducted in every clinical center on a monthly basis; (3) regular training is provided to the researchers; (4) a semiannual meeting is held to summarize the research and solve any problems in the study; (5) regular censoring is conducted by the CRO; and (6) the statistical experts will follow-up with this program and evaluate the credibility and effectiveness of the data.

In addition, this project establishes a Project Management Committee that is responsible for project design and implementation, summary and analysis of the data, and writing the research report. The following institutions are also established: (1) The Central Biological Specimen Bank and Central Laboratory is established to store, test and manage the specimens. Gene and biomarker detection are conducted in the central laboratory following unified standards. (2) The Medical Image Analysis Center is established to analyse, store and manage the DICOM data. A uniformed interpretation standard of medical imaging data is made by the MIAC. (3) The Information Managing Center is responsible for the construction and maintenance of the EDC system and ensuring the security, completeness and accuracy of the data.

Limitations also exist in this study. All of the participants are Chinese; thus, the conclusions can only represent the characteristics of the Chinese population. The credibility will be impaired if the conclusions are extrapolated to other races.

In addition, information asymmetry exists. For example, regular medical examinations are not widely implemented in some remote areas. In some remote areas, patients cannot arrive at the hospital in time when the aneurysm ruptures. The incidence rate of these occurrences remains unclear. For these populations, the rupture rate might be miscalculated in this study.

Moreover, there is a serious over-treatment phenomenon in the treatment of UIAs in China, which might affect the accuracy and authenticity of our conclusions about the rupture rate. From another perspective, this study will provide solid evidence that can be used to control the overtreatment phenomenon in China.

In conclusion, this is the first nationwide study aimed at creating a database of UIAs and describing the natural course of UIAs in China. It will provide evidence to guide the choice of the most appropriate management for specific UIA patients with different risk factors.

## Data Availability

Not applicable. This manuscript does not contain any data.

## Abbreviations

BSB: Biological Specimen Bank
CIAP: China Intracranial Aneurysm Project
CRA: clinical research associate
CRC: clinical research coordinator
CRF: case report form
CRO: Contract Research Organization
CT: computed tomography
CTA: computed tomography angiography
DBA: database administrator
DSA: digital subtraction angiography
EDC: electronic data capture
IA: intracranial aneurysm
IMC: Information Managing Center
ISUIA: International Study of Unruptured Intracranial Aneurysms
MIAC: Medical Image Analysis Center
MRA: magnetic resonance angiography
MRI: magnetic resonance imaging
PMC: Project Management Committee
ROC: receiver operating characteristic curve
SAH: subarachnoid hemorrhage
UCAS: Unruptured Cerebral Aneurysms Study
UIA: unruptured IA
